### Health Economic Evaluation

The health economic evaluation will include a cost-effectiveness analysis (CEA) and a cost-utility analysis from a societal perspective. An incremental cost-efficacy ratio (ICER; additional costs per additional person walking 10,000 steps/day) and an incremental cost-utility ratio (ICUR; additional cost for an additional QALY gained) will be determined. The outcome of the CEA is based on the primary outcome of the intervention and will be taken from the step counter measurement. QALYs will be calculated based on the EQ-5D-5L [44], which is a widely used standardized instrument to assess health-related quality of life. The EQ-5D-5L is evaluated using a German tariff to obtain preference weights [55]. As the intervention might influence people beyond health, we will also consider capability well-being using the ICEpop CAPability measure for adults (ICECAP-A) [48]. We will use a UK scoring tariff because a German tariff does not exist yet [56] and compare utilities based on capabilities with those based on QALYs.

The costs considered in the health economic evaluation comprise costs related to the development and provision of the intervention (eg, print-based materials, website, and time associated with the development of the intervention as opportunity costs), health care use (physician’s visits, contact with therapists, hospital stays, and rehabilitation), and costs associated with PA behavior (devices to support PA, membership fees [eg, gym membership], disability to work, and patient time). Productivity loss due to disability to work is calculated based on the human capital approach [57]. In a sensitivity analysis, patient time associated with PA, evaluated via opportunity costs, will also be examined. A discounting of costs and outcomes is not planned because of the short study duration.

The analysis will be performed according to the intention-to-treat principle. In the base case analysis, missing values will be imputed via multiple imputation. To make the random samples from the intervention and control region comparable, propensity score matching in the form of a weighted regression model will be applied after the imputation and for each imputed data set as suggested by Al-Janabi et al [58]. Covariates used for the matching will be the number of steps taken at baseline, age, gender, level of education, and household income.

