Mean incremental costs and the mean incremental outcome of the CEA will be estimated by a using a Generalized Linear Model with gamma distribution and log link function. To estimate the mean incremental outcome of the CEA (an additional person who walks 10,000 steps/day), a Generalized Linear Model with binomial distribution and logit link function will be estimated. Bootstrap procedures will be used to calculate 95% significance intervals for the ICER and ICUR [59,60]. To investigate uncertainty surrounding the ICER and ICUR, cost-effectiveness and cost-utility planes will be generated [61,62].

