## Results

Funding for this study was obtained in March 2020. Recruitment for this study and baseline data collection were conducted from May 2021 to March 2022 (as of March 2022, 626 participants were enrolled in the study). The intervention is being implemented in Duesseldorf for 1 year from April 2022 onward, and follow-up assessments will be conducted, starting in May 2023 (until September 2023). Data analysis will be performed in fall 2023, and the results will be published in spring 2024.

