## Discussion

### Anticipated Principal Findings

To the best of our knowledge, this is the first study in Germany aimed at replicating the effects of a complex intervention for PA promotion previously shown to be effective in another European country. The study findings will contribute to the growing body of evidence in Germany concerning the role of complex community-based interventions for the promotion of PA in the general population [19-27]. We anticipate to obtain results similar to those reported in the original study, where adults exposed to a complex PA intervention for 1 year displayed a greater increase in daily step count (ie, average of daily steps walked increased by 896 in intervention vs no increase in the comparison city) and were more likely to reach the WHO recommendation for PA than controls (ie, 8% increase in the number of individuals reaching the recommended 10,000 steps) [14]. With regard to the expected results of the process evaluation, we foresee that the processes involved in the implementation of the various intervention components may be somewhat different, as the organizational structures of administrative offices and community organizations in Germany may operate differently compared with Belgian organizations. However, by using a similar approach to monitoring processes, we expect to be able to compare our results with those obtained in the Ghent study. Furthermore, similar to the health economic evaluation of the original intervention indicating that the intervention was cost-saving [63], we expect “10,000 Steps Duesseldorf” to be cost-effective. Other previous health economic evaluations of population-level, community-based interventions addressing PA also demonstrated cost-effectiveness [64]. Finally, previous research suggests that community-based interventions involving local stakeholders in particular may yield intervention effects after the primary evaluation is completed [13,15,16]. Our study was preceded by a 6-month participatory planning phase involving key stakeholders of PA promotion in the city of Duesseldorf. Therefore, it is conceivable that the effects may become visible after the completion of the 1-year follow-up in our study.

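### The planned 95% bootstrap intervals on the ICER and ICUR ratios may not be readable as better or worse value if replicates span more than one quadrant; net monetary benefit from the same replicates avoids this

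*Protocol article*

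**What the plan says.** The Health Economic Evaluation section of the protocol article defines two ratios. The ICER is "additional costs per additional person walking 10,000 steps/day" and the ICUR is "additional cost for an additional QALY gained". For uncertainty it commits to two outputs. The first is an interval on each ratio: "Bootstrap procedures will be used to calculate 95% significance intervals for the ICER and ICUR". The second is graphical: "To investigate uncertainty surrounding the ICER and ICUR, cost-effectiveness and cost-utility planes will be generated". The section does not name the type of bootstrap interval, does not say how replicates with a zero or negative effect difference are treated, and mentions neither net monetary benefit nor an acceptability curve.

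On expected size, Anticipated Principal Findings looks for results like those of the original Belgian study: "8% increase in the number of individuals reaching the recommended 10,000 steps" and "average of daily steps walked increased by 896 in intervention vs no increase in the comparison city". It also notes that the original intervention was found to save costs. No QALY effect, QALY SD, cost SD or base proportion at 10,000 steps is given. The Results section reports "as of March 2022, 626 participants were enrolled in the study".

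**The concern.** An interval on a cost-effectiveness ratio can be read only while nearly all replicates lie in one quadrant of the plane. Across quadrants the sign of the ratio is ambiguous:

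- **Positive ratio:** dearer-and-better, or cheaper-and-worse.
- **Negative ratio:** cheaper-and-better (dominant), or dearer-and-worse (dominated).

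Any limit obtained by ranking ratios then mixes opposite conclusions. There are two routes to this. The effect difference may be small relative to its standard error, or the cost difference may be near zero. The second mixes quadrants even if every replicated effect difference is positive. It matters here because the original programme was cost-saving and similar results are anticipated. The planes show the scatter but give no interval and no probability of cost-effectiveness. At stake is whether the decision makers whom the article addresses can read the reported uncertainty. The primary step-count comparison is not affected.

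**Working it through.** **Plan's own figure.** None is stated for these intervals. The sample-size figure was checked because it supplies a favourable n: a difference of 1000 steps, SD 4500, 80% power and a two-sided 5% *t* test give 318.84, so 319 per city and 638 in total. This agrees with the Sample Size Calculation.

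**Inputs from the document.** 626 enrolled and 25% expected dropout: 626 × 0.75 / 2 = 234.75, about 235 per city. Anticipated gain of 8%, read here as percentage points.

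**Assumed inputs.** Base share at 10,000 steps 20–40%; QALY SD 0.10–0.20; QALY gain 0.005–0.02; no adjustment or weighting; normal approximation.

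**Formulas.** P(difference ≤ 0) = Φ(−d/SE). For proportions, SE = √{[p(1−p) + (p+d)(1−p−d)]/n}. For QALYs, SE = SD·√(2/n).

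**ICER denominator, 235 per city**

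| Base share | Gain | SE | d/SE | P(≤ 0) |
|---|---|---|---|---|
| 20% | 8 points | 0.0392 | 2.04 | 2.1% |
| 40% | 8 points | 0.0456 | 1.75 | 4.0% |
| 40% | 5 points | 0.0455 | 1.10 | 13.6% |
| 40% | 4.3 points | 0.0455 | 0.94 | 17.2% |

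The 4.3 points scale 8 by the ratio of two effects quoted in the Introduction: the pooled 554 steps and the Belgian difference 896 + 135 = 1031, so 8 × 554/1031 = 4.3. This is only a rough guide, since a share above a threshold need not move in proportion to mean steps.

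P(≤ 0) is also the share of replicates at or below zero in a trial that observes exactly the true gain, and hence the median share over trials. The mean share is larger, Φ(−d/(SE·√2)): 7.5% and 10.8% in the first two rows. The share exceeds 2.5%, one tail of a 95% interval, with probability Φ(1.96 − d/SE): 47% and 58%.

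**ICUR denominator, 235 per city**

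| QALY SD | SE | gain 0.005 | gain 0.01 | gain 0.02 |
|---|---|---|---|---|
| 0.10 | 0.0092 | 29.4% | 13.9% | 1.5% |
| 0.15 | 0.0138 | 35.9% | 23.5% | 7.4% |
| 0.20 | 0.0185 | 39.3% | 29.4% | 13.9% |

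**Second route: costs near zero.** Illustration with an assumed cost difference of 100 and SD 3000 (SE = 3000·√(2/235) = 277), independent of an 8-point effect at base 40%. P(cost difference ≤ 0) = Φ(−0.361) = 35.9%. The replicates split as follows:

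- dearer-and-better 61.5%
- dominant 34.5%
- dominated 2.5%
- cheaper-and-worse 1.4%

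Ranking the ratios in simulated normal draws gives limits of about −15,400 and 21,600. Of all negative ratios, 93% are dominant (34.5 / (34.5 + 2.5)). Yet the ratios beyond the lower limit are about half dominant (48%) and half dominated (52%). The lower limit therefore does not mark the better-value end of anything.

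**The case against.** The strongest reply has five parts.

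1. **Interval type.** A reader might infer that percentile intervals are planned. The text does not say so, and the type and the handling of awkward replicates commonly belong in an analysis plan that is not shown. This stands as far as it goes. But the article does fix the interval on the ratio itself, and any method that ranks ratios inherits the difficulty.
2. **Size.** A reader might infer that many replicates will have a non-positive effect difference. At the anticipated 8 points the ICER share in a typical trial is only 2–4%, and the larger means are pulled up by trials with a low observed effect. The ICUR figures rest wholly on assumed inputs; at a gain of 0.02 and SD 0.10 the probability is 1.5%. This stands.
3. **Pessimistic n and SE.** Multiple imputation is planned, and 235 per city is a lower figure. With all 626 (313 per city), 40% against 48% gives SE 0.0396 and P(≤ 0) of about 2%. Balancing baseline steps may reduce variance, while uneven weights may increase it; the net direction is unknown. This also stands.
4. **The planes.** If they plot the bootstrap replicates, quadrant shares can be read from them. That is a partial answer, but it supplies neither an interval nor a probability of cost-effectiveness.
5. **Omission.** The absence of net benefit from a condensed article is not itself an error. Agreed; the point concerns the method that is stated.

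**Conclusion.** The point holds conditionally. The article commits to intervals on two ratios, and these cannot be read as better or worse value if replicates span more than one quadrant. A reader might go further and conclude that the intervals will certainly be uninterpretable. The documents do not support that, because it depends on the observed cost and effect differences.

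The problem is likely for the ICUR if the one-year QALY gain is as small as 0.005–0.01 (14–39% under the assumed SDs) and less so at 0.02 (1.5–14%). It is possible for the ICER: about 2–4% at the anticipated 8 points and 14–17% at 4.3–5 points. If the 8% is a relative increase, the absolute gain would be smaller and the risk higher. A small or negative cost difference adds to the risk for both ratios whatever the effect. This is a cheap improvement to a secondary economic analysis.

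**What to change.** In Health Economic Evaluation, replace the sentence on ratio intervals with the following.

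- Report incremental net monetary benefit, λ × effect difference − cost difference, with a bootstrap 95% CI over a stated range of willingness to pay (λ), once for QALYs and once for an additional person reaching 10,000 steps.
- From the same replicates, give cost-effectiveness acceptability curves and the share of replicates in each quadrant.
- Keep the ICER and ICUR as point estimates with the planned planes.
- Give an interval on a ratio only if essentially all replicates lie in the quadrant of higher cost and higher effect.

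This needs no new data and no additional bootstrap. The cost is a change of wording and the need to state willingness-to-pay ranges in advance, including one for an additional person reaching 10,000 steps. The article gives no value for either.

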## Results

Funding for this study was obtained in March 2020. Recruitment for this study and baseline data collection were conducted from May 2021 to March 2022 (as of March 2022, 626 participants were enrolled in the study). The intervention is being implemented in Duesseldorf for 1 year from April 2022 onward, and follow-up assessments will be conducted, starting in May 2023 (until September 2023). Data analysis will be performed in fall 2023, and the results will be published in spring 2024.

## Discussion

### Anticipated Principal Findings

To the best of our knowledge, this is the first study in Germany aimed at replicating the effects of a complex intervention for PA promotion previously shown to be effective in another European country. The study findings will contribute to the growing body of evidence in Germany concerning the role of complex community-based interventions for the promotion of PA in the general population [19-27]. We anticipate to obtain results similar to those reported in the original study, where adults exposed to a complex PA intervention for 1 year displayed a greater increase in daily step count (ie, average of daily steps walked increased by 896 in intervention vs no increase in the comparison city) and were more likely to reach the WHO recommendation for PA than controls (ie, 8% increase in the number of individuals reaching the recommended 10,000 steps) [14]. With regard to the expected results of the process evaluation, we foresee that the processes involved in the implementation of the various intervention components may be somewhat different, as the organizational structures of administrative offices and community organizations in Germany may operate differently compared with Belgian organizations. However, by using a similar approach to monitoring processes, we expect to be able to compare our results with those obtained in the Ghent study. Furthermore, similar to the health economic evaluation of the original intervention indicating that the intervention was cost-saving [63], we expect “10,000 Steps Duesseldorf” to be cost-effective. Other previous health economic evaluations of population-level, community-based interventions addressing PA also demonstrated cost-effectiveness [64]. Finally, previous research suggests that community-based interventions involving local stakeholders in particular may yield intervention effects after the primary evaluation is completed [13,15,16]. Our study was preceded by a 6-month participatory planning phase involving key stakeholders of PA promotion in the city of Duesseldorf. Therefore, it is conceivable that the effects may become visible after the completion of the 1-year follow-up in our study.

### Comparison With Prior Work

As outlined earlier, the primary focus is on the comparison with the Ghent- and Rockhampton-based studies. Furthermore, we expect that the recommendation and use of step counters will be associated with a similar increase in daily steps walked, as was previously reported in several reviews and meta-analyses synthesizing the results of studies examining the effects of population-based PA interventions [11,13]. The analysis of the accelerometer data of the subsample in our study will allow us to analyze weekly minutes spent on MVPA and compare the results to those reported by Wahlich et al [13] in their review and meta-analysis.

### Strengths and Limitations

A major strength of this study is the use of an innovative methodological approach for examining the effects of a complex community-based PA intervention in Germany and the ability to compare the results obtained in this study to those reported in 2 other countries in 2 continents. To our knowledge, this is the first study to examine the effect of a multistrategy population-level intervention on PA behaviors targeting individuals aged ≥18 years, which was developed based on a participatory approach. Another strength is the use of objective measurements in a subsample of the study, allowing for the validation of the questionnaire data collected in the telephone-based interviews. A limitation is that, unlike in the original study, 2 entire cities could not be compared in terms of PA behavior of participants living in them. However, by balancing the city districts of both cities included in our study using indicators of socio-spatial deprivation, we hope to have obtained a similar sociodemographic composition of our study participants. Another limitation is the ongoing COVID-19 pandemic, which complicated the recruitment of study participants. Adjustments in the number of potential study participants contacted and invited to participate were necessary to offset the difficulties in enrolling participants to the study. Finally, in our study, a trial-based health economic evaluation is conducted that does not include modeling of long-term effects and costs. Nevertheless, the health economic evaluation will provide detailed information to decision makers regarding short-term cost-effectiveness of the intervention.

### Future Directions

Should this study reveal positive effects on PA in the intervention compared with the control city districts, conducting a 4-year follow-up to assess the long-term effects of the intervention on PA and quality of life, similar to Cocker et al [15], may be useful to demonstrate long-term effects. Furthermore, comparing the results of the 3 studies conducted in Rockhampton, Ghent, and Duesseldorf may help devise recommendations for adaptation and implementation in other European cities. In Germany, a rollout of the intervention in other cities (possibly starting with the control city, Wuppertal) could be a next step after the completion of the primary evaluation. A plan for scale up or dissemination will be developed at the end of the project. In the original Ghent-based study, the intervention was rolled out in all of Flanders and evaluated based on the RE-AIM framework [14]. A similar approach could be taken after completion of this study (eg, in the entire state of North Rhine-Westphalia or in an additional German state). Following the original study by Dubuy et al [18], combined baseline data from Duesseldorf and Wuppertal from this study could serve as a historical control group. Finally, future research may also include health economic modeling techniques that could shed further light on the long-term effects of intervention participation on cost-effectiveness of this multistrategy approach for PA promotion at the community level.

## Appendix

Multimedia Appendix 1 Informed consent materials.

Multimedia Appendix 2 List of covariates in the propensity score model.

Multimedia Appendix 3 Review Proposals.

Multimedia Appendix 4 Answers to Reviewers.

## Abbreviations

AEQUIPA: Physical Activity and Health Equity: Primary Prevention for Healthy Ageing
CEA: cost-effectiveness analysis
HLCA: Health Literacy in Childhood and Adolescence
ICECAP-A: The ICEpop CAPability measure for adults
ICER: incremental cost-efficacy ratio
ICUR: incremental cost-utility ratio
MVPA: moderate to vigorous physical activity
NAKO health study: National Cohort health study
PA: physical activity
QALY: quality-adjusted life year
REDCap: Research Electronic Data Capture
WHO: World Health Organization
